## Abstract

**Background:**

Type 2 diabetes can negatively impact long term health outcomes, healthcare costs and quality of life. However, intensive lifestyle interventions, including the Diabetes Prevention Program (DPP), can significantly lower risk of incident type 2 diabetes among overweight adults with prediabetes. Unfortunately, the majority of adults in the US who are at risk of developing diabetes do not engage in DPP-based lifestyle change programs. Increased adoption of evidence-based obesity and diabetes prevention interventions, such as the DPP, may help large employers reduce health risks and improve health outcomes among employees. In 2018, the University of California Office of thePresident (UCOP) implemented the UC DPP Initiative, a novel, multi-component program to address diabetes and obesity prevention across the UC system.

**Methods:**

The goal of our study is to conduct a multifaceted evaluation of the UC DPP Initiative using the Reach, Effectiveness, Adoption, Implementation, and Maintenance (RE-AIM) framework. Our evaluation will integrate unique and diverse UC data sources, including electronic health record (EHR) data, administrative claims, campus-based DPP cohort data, qualitative interviews and site visits. Our primary outcome of interest is the mean percent weight change among three groups of overweight/obese UC beneficiaries at risk for diabetes at 12-month follow-up. Secondary outcomes include mean percent weight change at 24-month follow-up, barriers and facilitators associated with implementatio, as well as  the degree of program adoption and maintenance.

**Discussion:**

Our study will help inform diabetes and obesity prevention efforts across the UC system. Findings from this evaluation will also be highly applicable to universities and large employers, as well as community organizers, healthcare organizations and insurers implementing the DPP and/or other health promotion interventions.

## Background

Type 2 diabetes is a chronic and often progressive disease that can lead to devastating complications and long-term disability [1]. The economic cost of diabetes is rising steeply, increasing from $245 billion in 2012 to $327 billion in 2017 [2]. The burden of diabetes on affected individuals and on society as a whole underscores the importance of prevention. The Centers for Disease Control and Prevention (CDC) estimate that up to 88 million adults aged 18 years or older have prediabetes, [1] and many of these individuals will progress to incident type 2 diabetes over 3 years without intervention [3, 4]. However, intensive lifestyle interventions (ILIs), including the Diabetes Prevention Program (DPP), can significantly lower risk of incident type 2 diabetes among overweight/obese adults with prediabetes [4]. Increased work-site adoption of obesity and diabetes prevention interventions, such as DPP-based ILIs, can help promote healthy weight among employees, [5, 6] reduce health risks, and improve health outcomes [6]. In a 2017 review of work-site translations of DPP, weight loss ranged between 1.4 and 4.9 kg at 7 to 12 months (*n* = 6 studies), with worksite programs offering > 16 core sessions having the most favorable outcomes [7].

Ongoing efforts to disseminate DPP nationally have increased the rate of program adoption by US employers, but reach and engagement among at-risk individuals remains relatively low [8]. University systems represent a promising, largely untapped option for DPP dissemination to overweight/obese adults with prediabetes. In the US, there are over 4300 higher education institutions (e.g., universities and colleges that grant degrees), [9] and in many communities, universities are the largest employer. The University of California (UC) system, for example, is one of the largest employers in California with over 229,000 employees [10]. University employee turnover may be lower than at for-profit organizations and many employees may also be enrolled in university-managed insurance programs, providing increased impetus to prevent diabetes and obesity. Large university systems also have many resources to readily implement DPP-based ILIs, making them an ideal setting to engage personnel in evidence-based obesity and diabetes prevention interventions. However, very few studies have examined the effectiveness of university-based DPP models. Among 1863 CDC registered DPP organizations as of March 1, 2021, 50 appear to be university or college-affiliated programs (Fig. 1). To our knowledge, only six published studies have focused on university based DPP adaptations. However, these studies included small sample sizes, pre-post analyses that lacked comparator groups, and short-term follow-up windows (Table 1) [11–16].

**Fig. 1 Fig1:**
[figure not shown]
University-based Diabetes Prevention Program with full and preliminary recognition from the Centers for Chronic Disease Prevention and Control (CDC) https://nccd.cdc.gov/DDT_DPRP/Registry.aspx

**Table 1 Tab1:** Published DPP translation studies

Study, Year	Site	Study design	Outcomes of interest	N	Follow up	Mean weight loss	Implementation implications
﻿A Worksite Diabetes Prevention Program Two-Year Impact on Employee Health, 2006 [11]	﻿BD Medical, Sandy, Utah	﻿Within- group study design	﻿Weight, body mass index, waist circumference, oral glucose tolerance testing, fasting insulin, blood lipids, and aerobic fitness	22 (8 M, 14 F)	2 years	0.76 lbs.	N/A
*A Randomized Controlled Trial Translating the Diabetes Prevention Program to a University Worksite, Ohio, 2012–2014, 2016 [12]	﻿Ohio State University	Pretest–posttest control group design	﻿Primary outcome was percentage weight change; secondary outcomes were height, waist circumference, Biometrics, dietary intake, and PA levels	35	3 months	5.1 lbs.	﻿N/A
*Early Weight-Loss Success Identifies Non-responders after a Lifestyle Intervention in a Worksite Diabetes Prevention Trial, 2015 [13]	﻿Ohio State University	Pre and post intervention in randomized experimental group	﻿Percent weight loss	32 (5 M, 27 F)	4 months	﻿16.7 lbs. in those who lost > 5% weight & 5.6 lbs. in those who lost < 5% weight	N/A
*A translational worksite diabetes prevention trial improves psychosocial status, dietary intake, and step counts among employees with prediabetes: A randomized controlled trial, 2015 [14]	Ohio State University	﻿Randomized pretest/posttest control group design	﻿Psychosocial outcomes including self-efficacy for eating a low fat (LF) diet and PA, goal commitment and difficulty, employee ﻿presenteeism, social support, problem solving.	35	3 months	N/A	﻿N/A
Putting the National Diabetes Prevention Program to Work: Predictors of Achieving Weight-Loss Goals in an Employee Population, 2019 [15]	﻿Vanderbilt University Medical Center	﻿Exploratory analysis of data from DPP participants enrolled in the first 5 cohorts	﻿Primary outcome was characteristics and program metrics for DPP participants.	165	12 months		﻿Session attendance and physical activity independently predicted achievement of the 5% weight-loss goal in this worksite translation of the DPP.
Mixed methods study of engagement in behaviors to prevent type 2 diabetes among employees with pre-diabetes, 2016 [16]	﻿University of Michigan	Pre and post mixed methods study	﻿Facilitators of and barriers to engagement in recommended behaviors	82 (23 M, 59 F)	3 months	N/A	﻿Key facilitators of engagement included assistance and encouragement from social networks as well as use of external supports such as tracking devices. Barriers to engagement included competing demands and insufficient resources ﻿for healthy behaviors.

Beginning in 2018, the UC System  implemented the UC DPP Initiative, which is a multi-component program to target diabetes and obesity prevention among at risk affiliates. This initiative was informed by a pilot DPP implemented at the University of California Los Angeles (UCLA) in 2016. UCLA DPP was one of the first university-based programs in the US to achieve full CDC recognition. CDC recognition is granted to programs that meet all recommended milestones for DPP delivery, including 5% mean weight loss among participants. Based on the success of the UCLA campus-wide DPP, campus leaders and researchers partnered with the UC Office of the President (UCOP) and UC Health to launch a UC-wide DPP Initiative in 2018. By 2019, all 10 UC campuses had implemented UC DPP, which now operates as part of routine campus activities (more details below). To our knowledge, this is one of the largest university-based efforts to adress diabetes and obesity prevention with a focus on system-wide DPP-based ILI delivery.

Our goal is to conduct a rigorous, mixed-methods evaluation of the UC DPP Initiative, focusing on the five UC campuses with large medical centers where robust EHR data for UC beneficiaries is also available; namely UC Los Angeles, Irvine, San Diego, San Francisco, and Davis. Our goals are to identify why the UC DPP Initiative succeeds (or not), and to document lessons learned across the UC system and between campuses to inform future efforts across UC and other large university systems.

### The University of California Diabetes Prevention Program (UC DPP) initiative

The UC DPP Initiative has four key components; 1) identification of diabetes prevention as a system-wide goal, 2) a prediabetes awareness campaign targeting at-risk beneficiaries, 3) coordinated DPP implementation and delivery on every UC campus 4) coverage of DPP for all campus affiliates, including faculty, staff and students, at no cost. Each campus identified local champions, engaged key stakeholders, and signed a Memorandum of Understanding (MOU) with UCOP to receive funding for program implementation. The MOU outlined a commitment to the goals of the initiative, delineated guidelines for DPP delivery, and confirmed available resources. Funding to campuses was based on fixed costs of delivering a DPP cohort (i.e., not based on number of participants or program outcomes). Although the UC system could have easily continued to outsource DPP delivery (as many universities and workplaces do through their insurers), this initiative aimed to prioritize diabetes prevention as a highly visible system-wide goal that leverages university-based infrastructure and resources to implement all four key components. For example, campuses aimed to implement > 4 DPP cohorts in their first 2 years and then receive additional UCOP funding to add cohorts based on local demand.

The UC DPP Coordinating Center was established by UCOP/UC Health to support system-wide DPP activities. The UC DPP Coordinating Center assists UC campuses with all aspects of program delivery, including DPP coach training by UCLA-based certified master trainers and data management for DPP cohorts. Centralizing some activities, such as coach training, provides efficiency of scale (e.g., each individual campus is not required to spend time and money to train master trainers). The Coordinating Center leads monthly group calls with all UC campuses and individual calls with each campus as needed. Each UC campus is also registered with the National DPP (each campus has their own unique CDC organization number in order to be eligible for CDC recognition).

The UC system, like many other academic institutions, provides and manages health insurance benefits for many of its employees. The UC DPP Coordinating Center conducts outreach to at-risk UC health insurance beneficiaries with documented prediabetes (i.e., prediabetes diagnosed as part of usual care). Trained UCOP staff use UC EHR and claims data algorithms to identify at-risk participants with documented prediabetes. Personalized initiation letters with UC DPP logos are mailed from the Coordinating Center to overweight/obese UC beneficiaries with documented prediabetes. These prediabetes awareness letters include information about the importance of diabetes prevention and the UC DPP Initiative, including contact information for the local campus DPP. The letters clarify that there is no out-of-pocket cost for the UC DPP. UC DPP cohorts are led by UC staff who complete DPP coach training and have experience delivering campus-based wellness programs. DPP eligibility criteria include 1) age > 18 years, 2) body mass index (BMI) > 25 kg/m^2^ (> 23 for Asian adults) and 3) history of prediabetes, gestational diabetes, or a “high risk” CDC Prediabetes Risk Test. UC funding is provided to campuses for each additional DPP cohort and is not contingent on meeting National DPP metrics (e.g., 5% weight loss).

## Methods

To ensure a rigorous and multifaceted program evaluation, we will use the reach, effectiveness, adoption, implementation, and maintenance (RE-AIM) evaluation framework. The RE-AIM framework is a well-established tool to evaluate the implementation process of evidence-based health promotion programs and interventions, to address internal and external validity, as well as feasibility and generalizability [17–19]. We propose a rigorous, comprehensive evaluation of the UC DPP Initiative integrating unique and diverse data sources including EHR data, administrative claims, and campus data (DPP data, site visits and qualitative interviews)**.** Table 2 provides an overview of the UC DPP-specific metrics guided by the RE-AIM framework. Our study includes three specific aims described in more detail below.

**Table 2 Tab2:** RE-AIM dimensions, questions and UC DPP-specific metrics

REAIM dimension & defining questions	UC DPP-specific metrics
Reach *What proportion of eligible participants a) were excluded, b) took part and c) how representative were those who participated?*	• Estimate persons reached based on the number eligible within each campus and across UC (received targeted outreach and enrolled in DPP) • Estimate persons engaged in DPP (attended > 9 and > 16 sessions) • Report exclusions, participation rates, drop-outs and representativeness within each campus and across UC
Effectiveness *What impact did the intervention have on a) all participants who began the program; b) on process and primary outcomes; and c) on both positive and negative (unintended) consequences?*	• Examine effectiveness (% weight change and DPP participation) within and between subjects (more detail below) • Examine consistency of outcomes across sites and key subgroups (e.g., race and ethnicity)
Adoption What proportion of stakeholders a) were excluded, b) participated and c) how representative were they?	• Assess representativeness of those making UC DPP related decisions with on each campus (i.e., those leading DPP efforts, implementation and maintenance) • Report types of key campus stakeholders involved within each campus and variations across UC
Implementation *To what extent were the various intervention components delivered as intended, especially when conducted by different non-research staff?*	• Assess facilitators and barriers to initiative implementation; examine how these vary across campuses and over time • Assess unintended consequences of implementation (i.e., support or resources pulled away from other programs) • Assess if UC DPP milestones are followed at all campuses or only partially implemented at some locations • Assess fidelity for at least two of 16 core DPP sessions at each campus • Assess similarities and differences in strategies across campuses (e.g., recruitment and engagement efforts, reported costs of program delivery)
Maintenance *To what extent was intervention maintained and what adaptations were required to maintain it? How was the original protocol modified? What was the attrition rate; were drop-outs representative?*	• Examine UC DPP outcomes within and across campuses, including attrition. • Report the degree to which UC DPP milestones were met over time • Report the degree to which initiative is integrated with campus workflow • Report whether the local and UC leadership provide upkeep and necessary support (e.g., staff)

*Adapted from RE-AIM [20, 21]

### Aim 1: effectiveness of UC DPP

To assess the effectiveness of the UC DPP Initiative, we will examine mean percent weight change from baseline at 12 month follow-up and 24 month follow-up within and between three groups of overweight/obese UC beneficiaries. Group 1 includes overweight/obese beneficiaries with documented prediabetes who receive UC DPP Initiative prediabetes awareness letters and enroll in DPP (i.e., receive “full treatment”). Group 2 includes overweight/obese beneficiaries with documented prediabetes who receive UC DPP Initiative prediabetes awareness letters, but do not enroll in DPP. Group 3 includes overweight/obese UC beneficiaries without documented prediabetes who are not included in the UC DPP Initiative (do not receive prediabetes awareness letters and do not enroll in DPP). Group 3 serves as a control group to account for secular trends and/or concurrent programs that may affect weight change outcomes among UC beneficiaries (such as weight management services any overweight/obese UC beneficiaries may receive as part of routine care). The primary outcome will be % weight change at 12-month follow-up within those who received a “full intervention dose” (i.e., Group 1) and secondary outcomes will compare mean % weight change between UC beneficiaries (Groups 1 vs. 2 and Group 1 + 2 vs. Group 3).

### Data collection & statistical analyses

To measure mean percent weight change, we will use EHR weights, which are collected similarly across UC health center visits, and DPP session weights for UC beneficiaries who enroll in DPP. Baseline covariate differences between those with and without attrition will be examined and we will then adjust for any covariates found to be significantly different (*p* < 0.05) between attrition groups in order to satisfy the Missing at Random assumptions of the mixed effects models. Because attrition could be a consequence of our primary outcome (i.e. weight) our missing data may be Missing Not at Random. In this instance we will utilize pattern mixture modeling to impute missing valuies. We will conduct within-subject analysis estimates of UC DPP Initiative effectiveness among those who received a “full intervention dose” (i.e., Group 1 prediabetes awareness letters and enrolled in DPP). For this primary analysis, we will use a mixed effects linear regression model to compare percent weight change within Group 1 subjects 12 and 24 months before DPP enrollment (pre period) and 12 and 24 months after enrollment (post period). Models for the trajectory of percent weight change will be specified with a random intercept for person with nested random slope for time from enrollment measured on a continuum. Average within-person between time-period (post vs. pre-enrollment) differences in the trajectory for % weight change will be modeled using a fixed effect interaction term of time-by-time-period to test for between time-period differences in the rate of % weight change. These models will be fit using a random intercept for person and random slope for time-period (post vs pre). A fixed effect of time-period will be used to estimate the average between time-period difference in % weight change adjusting for the corresponding length of time over which the change was observed. For both models, exploratory post-hoc analyses will also consider additional subject level covariates (age, gender, race, ethnicity, number of co-morbidities, number of DPP sessions attended, education level and years employed at the institution), as well as DPP site. Interactions of the difference over time (rates or mean levels) by these subject characteristics or site will also be explored to evaluate whether there is a differential benefit of the program for certain groups of beneficiaries (i.e., heterogeneity in treatment effect) and across sites. In the presence of statistically significant (*p* < 0.05) interactions, the models will be stratified so as to allow for potential heterogeneity in the covariates as well.

We will also compare outcomes between UC beneficiaries in Groups 1 vs. 2, a between-subject comparison, to estimate DPP effectiveness while holding the effect of the prediabetes awareness campaign constant across groups (both Group 1 and 2 receive prediabetes outreach letters). The mixed effects models mentioned above will be modified to examine between group differences in within-person change by incorporating an interaction term with Group membership. Similarly, we will compare outcomes in Groups 1 + 2 vs. Group 3, a between-subject comparison akin to an intent-to-treat (ITT) analytic approach since outcomes are being assessed among all UC beneficiaries with documented prediabetes eligible to receive the UC DPP Initiative in comparison to similarly overweight/obese individuals not exposed to the program. We will use propensity score matching to identify comparable overweight/obese beneficiaries with (Groups 1 + 2) and without (Group 3) documented prediabetes. The propensity score model will include baseline age, gender, race/ethnicity, BMI, and medical co-morbidities. Matching will be accomplished through use of the nearest-neighbor algorithm. Between group balance in the propensity scores and covariates will additionally be examined. While Groups 1 and 2 have an easily defined baseline for differentiating between pre- and post- diabetes awareness (i.e., enrollment or awareness letter date), Group 3 will have their baseline selected as corresponding to 12–18 months (or 24–30 months) prior to their most recent EHR entry.

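### DPP session weights exist only for Group 1 from enrolment onward, so a session-versus-clinic offset can bias the primary pre/post contrast and the secondary Group 1 vs 2 contrast

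*Protocol article*

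**What the plan says.** Under Data collection & statistical analyses, the Protocol article names two sources for the weights behind the outcome: "we will use EHR weights, which are collected similarly across UC health center visits, and DPP session weights for UC beneficiaries who enroll in DPP". The remark on similar collection is attached to the health-center weights only. The article says nothing equivalent about weights taken at program sessions.

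The same section sets the primary model, which will "compare percent weight change within Group 1 subjects 12 and 24 months before DPP enrollment (pre period) and 12 and 24 months after enrollment". The Group 1 vs 2 comparison uses these mixed models with a group interaction added.

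Aim 1: effectiveness of UC DPP defines the groups. Group 2 members "receive UC DPP Initiative prediabetes awareness letters, but do not enroll in DPP"; Group 3 members "do not receive prediabetes awareness letters and do not enroll in DPP". Group 3's baseline is set by counting back a fixed interval "prior to their most recent EHR entry". Aim 1 makes the within-Group-1 change at 12 months primary, and Groups 1 vs 2 and Groups 1+2 vs 3 secondary.

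The covariates listed for exploratory post-hoc analyses include site and number of sessions attended, but not weight source.

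**The concern.** The second source is present only in the exposed group and only in the exposed period, which is where both contrasts look for the effect. If session weights read systematically higher or lower than clinic weights (different scales, clothing or time of day), the models as described cannot tell that difference from a weight change after enrolment. A larger sample does not reduce such a bias. The other safeguards do not reach it. The attrition adjustment and pattern-mixture modelling address missing weights, not differently measured ones. The propensity matching uses baseline characteristics and applies only to Groups 1+2 vs Group 3.

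**Working it through.** **Step 1. Where each source can occur** (from the group definitions and the data-source sentence)

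| Group | Before baseline | After baseline |
|---|---|---|
| 1 | EHR | EHR and session |
| 2 | EHR | EHR |
| 3 | EHR | EHR |

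A session weight might also serve as Group 1's enrolment baseline; the article does not say.

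**Step 2. Where an offset lands.** Suppose session weights read lower than clinic weights by d% of body weight. To first order:

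- *EHR baseline, session follow-up:* the pre-period change is unaffected and the post-period change shifts by −d. The post-minus-pre contrast shifts by −d (loss exaggerated), and so does Group 1 vs 2.
- *Session baseline, session follow-up:* d cancels in the post-period change. The pre-period change, from an earlier EHR weight to the session baseline, shifts by −d, so post minus pre shifts by +d (loss understated). Group 1 vs 2 is unaffected if only post-period changes are compared. It is affected if, as planned, the within-person pre/post difference is compared.
- *EHR throughout:* no shift.

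If session weights read higher, every sign reverses. If only a fraction f of follow-up weights are session weights, the follow-up shift is about f × d.

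**Step 3. The plan's own power figures** (Sample size and power calculations). No SD is given, so it is solved from the stated detectable differences at two-sided alpha 0.05.

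- Primary, N = 50, 80% power at 3.3%. Normal approximation: SD = 3.3 × √50 / (1.960 + 0.842) = 8.33; with the t distribution, 8.16. Power at 5% is then 98.9%, which agrees with the stated value of over 98%.
- Group 1 vs 2, 50 vs 500, 80% power at 2.5%. SD = 2.5 / [√(1/50 + 1/500) × (1.964 + 0.842)] = 6.01. Power at 3% is then 92.0%, close to the stated 90%.

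The figures reproduce and are not in question. They serve only to scale the offset.

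**Step 4. Size under assumed offsets.** The range 0.5% to 2% is an assumption; nothing in the article supports a particular value. The standard errors are 8.16/√50 = 1.15 points (primary) and 6.01 × √(1/50 + 1/500) = 0.89 points (Group 1 vs 2). The last two columns give the chance that a nominal 5% test rejects when there is no true effect. They use simple t-tests as stand-ins for the mixed models.

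| Offset d | Share f | Shift (points) | Share of 5% target | Share of 3% difference | Primary | Group 1 vs 2 |
|---|---|---|---|---|---|---|
| 0.5% | all | 0.5 | 10% | 17% | 7% | 9% |
| 1% | half | 0.5 | 10% | 17% | 7% | 9% |
| 1% | all | 1.0 | 20% | 33% | 14% | 20% |
| 1.5% | all | 1.5 | 30% | 50% | 25% | 39% |
| 2% | all | 2.0 | 40% | 67% | 40% | 61% |

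**Step 5. Groups 1+2 vs Group 3.** Group 1 is 50 of 550, so a 1-point shift is diluted to 1 × 50/550 = 0.09 points, against a stated detectable difference of 1.1%.

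**The case against.** The strongest reply is that this is a condensed journal article. The rule for which source supplies baseline and 12-month weights, and any sensitivity analysis, may sit in a fuller plan. That stands as far as it goes: the missing rule is not itself the fault, and no quoted sentence is false. What the article does fix is the use of a second source for enrollees alone, with comparability stated only for the other source.

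A reader might infer that the primary estimate is certainly biased, and in the program's favor. The documents do not support that. Whether session weights differ at all from clinic weights is unknown, and Step 2 shows that the sign depends on an unstated baseline source. One of the two planned models also tests the rate of change, and an offset that is constant throughout the post period moves the level rather than the slope.

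A reader might also infer that source and exposure are fully confounded. They are not, because Group 1 members are beneficiaries who can have EHR weights after enrolment.

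It is also true that session weights depend on attendance, and that the article plans attrition adjustment, pattern-mixture modelling and exploration of sessions attended. These bear on selective follow-up but do not remove an offset between scales.

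**Conclusion.** The concern holds as a structural weakness of the stated measurement rule. The outcome is measured with an additional source only in Group 1 from enrolment onward, and the described models do not separate the sources. A systematic offset can therefore bias the primary post-versus-pre contrast and the secondary Group 1 vs 2 contrast.

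Its size and direction cannot be derived from the documents. With an assumed 1% offset, a computed change shifts by up to 1 percentage point, and by about half that if half of the follow-up weights come from sessions. This matters most for Group 1 vs 2, where the anticipated difference is 3%. Groups 1+2 vs Group 3 is little affected and needs no change on this account. The point calls for a cheap improvement; it does not show that the primary analysis is invalid.

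**What to change.** 1. State which source supplies each weight, and use the same source for baseline and follow-up within each computed change.
2. Prespecify an EHR-weights-only analysis of the primary and Group 1 vs 2 contrasts, with identical time windows in both periods and all groups compared. Report it beside the result that uses both sources.
3. Where Group 1 members have a session and an EHR weight close in time, estimate the offset and add a source term to those two models.

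All three use data already planned for collection. The cost is fewer Group 1 weights, hence a wider interval in the EHR-only analysis, which also depends on who attends clinic. With about 50 people in Group 1 (10 per site), the offset will be estimated imprecisely. The source term should therefore support the EHR-only analysis and not replace it. Demanding that the conclusion also reach significance in the thinner EHR-only analysis would be a matter of preference and is not part of this recommendation.
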